# ‘Physio-EndEA’ Study: A Randomized, Parallel-Group Controlled Trial to Evaluate the Effect of a Supervised and Adapted Therapeutic Exercise Program to Improve Quality of Life in Symptomatic Women Diagnosed with Endometriosis

**DOI:** 10.3390/ijerph19031738

**Published:** 2022-02-02

**Keywords:** endometriosis, physiotherapy, therapeutic exercise, quality of life, motor control, pain

## Abstract

Aim: The ‘Physio-EndEA’ study aims to explore the potential benefits of a therapeutic exercise program (focused on lumbopelvic stabilization and tolerance to exertion) on the health-related quality of life (HRQoL) of symptomatic endometriosis women. Design: The present study will use a parallel-group randomized controlled trial design. Methods: A total of 22 symptomatic endometriosis women will be randomized 1:1 to the Physio-EndEA or usual care groups. The ‘Physio-EndEA’ program will consist of a one-week lumbopelvic stabilization learning phase followed by an eight-week phase of stretching, aerobic and resistance exercises focused on the lumbopelvic area that will be sequentially instructed and supervised by a trained physiotherapist (with volume and intensity progression) and adapted daily to the potential of each participant. The primary outcome measure is HRQoL. The secondary outcome measures included clinician-reported outcomes (pressure pain thresholds, muscle thickness and strength, flexibility, body balance and cardiorespiratory fitness) and patient-reported outcomes (pain intensity, physical fitness, chronic fatigue, sexual function, gastrointestinal function and sleep quality). Discussion: Findings of this study will help to identify cost-effective non-pharmacological options (such as this exercise-based intervention) that may contribute to the improvement of HRQoL in symptomatic endometriosis women.

## 1. Introduction

Endometriosis is considered among the most prevalent disease conditions in women of childbearing age. Although the numbers are still unknown, it has been estimated that 8–11% of women of reproductive age have endometriosis (with or without a clinical diagnosis) [1], counting for approximately 176 million affected women worldwide [2], with a peak incidence in women who are in their thirties and forties [3]. Moreover, this percentage increases, reaching 30–40%, when considering those women with a history of infertility [1]. It is an oestrogen-dependent female disease characterized by the proliferation of endometrial glands and stroma outside the uterine cavity [4]. In general, depending on the site of implementation, lesions can be differentiated into ovarian (ectopic tissue adhered to the ovaries), peritoneal or deeply infiltrating lesions [5].

Although endometriosis was described for the first time by Carl Von Rokitansky more than 150 years ago [6], little is known about the aetiology and pathogenesis of the disease and, therefore, about therapeutic options. Despite that some theories have tried to explain the development of these ectopic lesions [7], it is currently gaining recognition the endocrine-disrupting hypothesis that suggests that human exposure to synthetic chemicals with endocrine mimicking properties may be underlying the pathogenesis of endometriosis [8]. In this regard, it has been recently suggested that foetal exposure to diethylstilbesterol, a known endocrine-disrupting chemical, may underlie the development of endometriosis in adulthood [9]. In any case, an in situ chronic oxidative/inflammatory milieu originated by these ectopic lesions is frequently observed, which may lead to an altered microenvironment that includes, among others, the activation of epithelial-mesenchymal transition cell-signalling pathways [7]. Moreover, independently of their implementation site, endometriotic lesions are frequently detected to be vascularized and innervated [10,11]. The development of these nerve fibres (responsible for conveying nociceptive signals), but not the extent, location or type of endometriosis found at laparoscopy seems to be related to the severity of pain [12]. Hence, the affected women usually report dysmenorrhea (i.e., painful menstruation), dyspareunia (i.e., painful sexual intercourse), dyschezia (i.e., painful defecation), dysuria (i.e., painful urination) and, in general, chronic pelvic pain (i.e., pain perceived to originate in the pelvis lasting for longer than 6 months) [13].

In fact, pain, considered in its multiple versions, is acknowledged to be the most common and more disabling symptom of endometriosis [14,15], although the burden of endometriosis symptoms is highly variable between patients [16]. Pain is suggested to underlie the reduced level of physical activity [17,18], and the high prevalence of reported chronic fatigue [18,19,20], as well as the broad burden of disabilities described for some of these affected women [21]. In this regard, it has been published a relevant worse impact on everyday activities [21,22,23], sleep quality [14,17,20], relationship with their partner and reproductive planning [24,25], emotional and mental health [26,27], education [28,29], work productivity [30,31,32,33] or social life [28,29] that, in combination, leads to a significant reduction in health-related quality of life (HRQoL) [14,18,20,24,31,34]. Even more, endometriosis is acknowledged to be a risk factor for gynaecological cancer [4]. As a result, a systematic review confirms a substantial economic burden associated with endometriosis [35]. Although they greatly varied by country, direct costs (including inpatient, outpatient, surgery, drug and other healthcare service cost) ranged from USD 1109 per patient per year in Canada to USD 12,118 in the USA. Indirect costs (related to the loss of productivity at work) ranged from USD 3314 per patient per year in Austria to USD 15,737 in the USA [35].

In spite of the medical management of endometriosis having not been fully standardized worldwide, treatment schedules often include a palliative pharmacological control of pain symptoms (analgesics and oral contraceptives being the most commonly indicated) and surgery for resection of lesions, although with an elevated risk for recurrence [4]. Nevertheless, this therapeutic approach is clearly insufficient to manage the burden of symptoms in many women with endometriosis [4,36]. In this context, rehabilitation, through the vast array of therapeutic strategies for pain control might offer a substantial benefit to ameliorate pain-related disabilities and to improve HRQoL in endometriosis women. Indeed, a case–control study focused on visceral osteopathy [37], a retrospective study evaluating electrical muscle stimulation [38] and two randomized controlled trials exploring the potential benefits of pulsed high-intensity laser therapy [39] and yoga [40] have reported a significant improvement in HRQoL in these patients, although the contribution to individual occupational roles have not been addressed yet. Moreover, in contrast to osteopathy (with limited scientific evidence) or laser therapy (with non-standardized dosimetry), therapeutic exercise has been widely demonstrated to induce either soft tissue remodelling [41] and modifications in the nervous system [42], of particular interest in endometriosis given the elevated prevalence of central sensitization in these patients [43,44]. Additionally, it has been shown that regular physical exercise also exerts a protective effect against diseases that involve oxidative and/or inflammatory processes since it induces an increase in the systemic levels of mediators with anti-oxidant and anti-inflammatory properties [45]. In fact, a recent study has shown that the practice of regular physical exercise increases anti-oxidative responses in experimentally induced endometriosis in rats [46]. However, the limited number of publications lead the European Society of Human Reproduction and Embryology (ESHRE) to declare that the usefulness of physical practice for primary prevention of endometriosis is uncertain [47].

Chronic pelvic and visceral pain are typically referred to as somatic structures (skin, subcutis and muscle) leading to significant trophic changes of soft tissues, such as decreased muscle thickness [48], probably due to pain-derived physical inactivity. In this context, a vicious circle is often identified in which pain in the lumbopelvic area [17,49] leads to physical inactivity and thus to muscle deconditioning that potentially affects deep abdominal muscles (with a postural function), which, in turn, might jeopardize motor control of the lumbopelvic area [44], increasing pain and decreasing the capacity to carry out their occupational roles [21]. In particular, recent findings of our research group have identified a number of physical impairments in women with endometriosis, including reduced pressure pain thresholds (PTTs), flexibility, body balance, muscle thickness and/or muscle strength of the lumbopelvic and abdominal regions; lower lumbopelvic stability and functional capacity; and increased fatigue when compared with healthy women [18,44]. In spite of the fact that few studies have recently reported benefits of exercise on HRQoL in endometriosis patients [40,50], none of them have been focused on the stabilization of the lumbopelvic area. Thus, the global aim of the ‘Physio-EndEA’ study will be to explore the short- and long-term effects of a supervised tailored therapeutic exercise program on the HRQoL and health-related fitness on women with a clinical diagnosis of endometriosis and a history of clinical symptoms. This therapeutic exercise program has been designed to improve tolerance to exertion, endurance and flexibility, paying special attention to the lumbopelvic area in order to mitigate pain associated to a poor motor control. The present methodological article describes the study design, procedures and methods that will be conducted in this project.

## 2. Materials and Methods

### 2.1. Study Design and Setting

Encompassed in a multidisciplinary research project (EndEA, Endometriosis y Exposición Ambiental), the ‘Physio-EndEA’ study is a parallel-group randomized non-inferiority trial (ClinicalTrials.gov, NCT03979183) based on a 1 + 8-week exercise program that will be conducted in 26 patients diagnosed with endometriosis (*n* = 13 experimental group vs. *n* = 13 control group) in Granada (Spain). The organizational and participants flow is presented in Figure 1. Primary and secondary outcomes will be assessed at baseline and immediately after intervention. Moreover, we will also evaluate the long-term impact of this exercise program by a final assessment 1 year after intervention with similar characteristics to the post-program evaluation. Physio-EndEA will be carried out at CUIDATE unit (http://csaludable.ugr.es/pages/dossierultimo/%21, accessed on 15 June 2021), a research unit for rehabilitation in oncology and related diseases. The protocol has followed the recommendations of the Standard Protocol Items: Recommendations for Intervention Trials (SPIRIT) checklist [51,52], and Figure 1 shows the SPIRIT diagram. This study was approved by the Clinical Research Ethics Committee of Granada, Government of Andalusia, Spain (code: 0792-N-18). ‘Physio-EndEA’ study was registered with ClinicalTrials.gov (code: NCT03979183).

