#### 2.3.2. Usual Care/Control Group

Participants randomly assigned to the control group (*n* = 13) will receive the usual treatment, which is stipulated by their gynaecologist. Additionally, during the initial evaluation session, the trained physiotherapist assessor will offer general advice about the positive effects of physical activity and a healthy lifestyle for their HRQoL. For ethical reasons, control participants will be given the opportunity to participate in an exercise program with the same characteristics of this therapeutic exercise intervention after completion of this study, although their results will not be included in the analyses.

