### 2.6. Sample Size

The estimated sample size was determined for the primary outcome variable (HRQoL-pain) using the EHP-30 questionnaire and calculations from a previous study to detect a mean difference between control and intervention groups of 24.7 (28.4 ± 18.7 vs. 3.66 ± 18.4; Gonçalves, Barros and Bahamondes [40]). Assuming an α error of 0.05, a power of 85% and an effect size of 1.34 (based on the results of the reference study), we need a sample of 10 participants for each group. Assuming a possible 30% dropout rate, we will recruit a minimum of 13 participants per group (*n* = 26). G*Power v. 3.1 (Düsseldorf University, Düsseldorf, Germany) was used to calculate the sample size.

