### 2.9. Data Analysis

Since this study aims to determine the potential benefits of therapeutic exercise on the HRQoL of endometriosis patients, statistical analyses will be performed on an intention-to-treat basis. Only those participants that would have attended at least 75% of the sessions and completed at least two assessments (baseline and one evaluation of the two follow-ups) will be included in the analyses. The worst-case value will be used to replace missing data, after a previous reported procedure.

Mean and standard deviation will be used to describe variable scores at baseline and both follow-up measurements (postprogram and 1 year). Additionally, the Shapiro–Wilk test will be used to assess the normality of the distribution of the variables. To evaluate the ability of the randomization process to avoid differences between groups at baseline, Student’s t-test and chi-square test will be used to compare continuous and categorical data, respectively. An equivalent statistical approach will be conducted in case of non-parametrical data (Mann–Whitney and Kruskal–Wallis tests).

To evaluate the influence of treatment on outcome scores, a repeated-measure ANCOVA between the three time points (baseline, postprogram and 24 weeks later) will be used to examine the between-group and within-subject differences. Patient age, years since diagnosis, education level, marital status and the presence of heavy bleeding during the menstruation period will be used as covariates. To complete the analysis, we will report effect size (Cohen d) and level significance attending to interaction effects (group x time) to examine intergroup effects and to determine whether these were negligible (d < 0.2), small (0.2 < d > 0.5), moderate (0.5 < d > 0.8) or large (d > 0.8).

The statistical significance will be set at α = 0.05. Statistical analyses will be conducted on the Statistical Program for Social Sciences (IBM, SPSS 24.0).

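### Section 2.1 calls the trial non-inferiority, but its aim, sample size and test are those of a superiority trial

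*Protocol article*

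**What the plan says.** Section 2.1 (Study Design and Setting) says the study "is a parallel-group randomized non-inferiority trial". The word non-inferiority occurs nowhere else in the article.

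The other relevant sections describe a search for benefit:

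- **Aim.** The title and abstract speak of improving quality of life and of potential benefits. The Introduction gives the aim as "to explore the short- and long-term effects of a supervised tailored therapeutic exercise program on the HRQoL", and section 2.9 opens "Since this study aims to determine the potential benefits of therapeutic exercise on the HRQoL of endometriosis patients". The Discussion repeats the aim of benefit.
- **Comparator.** Under section 2.3.2, controls "will receive the usual treatment, which is stipulated by their gynaecologist", with general lifestyle advice in addition.
- **Sample size.** Section 2.6 sizes the trial "to detect a mean difference between control and intervention groups of 24.7" points on EHP-30 pain, from reference values "28.4 ± 18.7 vs. 3.66 ± 18.4". It continues "Assuming an α error of 0.05, a power of 85% and an effect size of 1.34" and concludes "we need a sample of 10 participants for each group". After the dropout allowance, 13 per group are to be recruited.
- **Test.** Section 2.9 specifies a repeated-measures ANCOVA for between-group and within-subject differences, with Cohen d and the group-by-time interaction judged at 0.05.

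**The concern.** A non-inferiority trial tests whether the new arm is worse than control by no more than a stated margin. A superiority trial tests whether it is better. The two have different null hypotheses, different sample-size formulae and different readings of a result that shows no difference. Section 2.1 declares the first kind, and the aim, sizing and test belong to the second.

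The Introduction and Discussion describe usual medical care as clearly insufficient for many patients and present exercise as something used in combination with it. Showing that the program is merely not worse than such a comparator would not answer the trial's question.

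At stake is the reading of a null result. In a trial this small, a non-significant difference is a realistic outcome. While the declared design says non-inferiority, nothing in the text stops a reader or a later author from taking that outcome as support for the declared hypothesis, although no margin was set against which to judge it.

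**Working it through.** **Inputs.** From section 2.6: means 28.4 and 3.66, SDs 18.7 and 18.4, α = 0.05 (sidedness not stated), power 85%, d = 1.34, 10 per group. From section 2.4.1: EHP-30 is scored 0–100, higher is worse.

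**Step 1. Effect size.** Pooled SD = √((18.7² + 18.4²)/2) = 18.55. Difference = 28.4 − 3.66 = 24.74. d = 24.74/18.55 = 1.33, close to the stated 1.34 (24.7/18.4 also gives 1.34).

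**Step 2. Reproduce the plan's 10 per group as a superiority calculation.** Two-sided normal approximation:

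n = 2 × (1.960 + 1.036)² / 1.34² = 10.0003 (unrounded z-values).

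This is the stated 10, or 11 on strict rounding up. It is a formula for detecting a difference, and no margin appears in it.

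**Step 3. Power under the t-test (noncentral t, d = 1.34).**

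| Completers per group | Two-sided 0.05 | One-sided 0.05 |
|---|---|---|
| 9 | 0.761 | 0.859 |
| 10 | 0.809 | 0.892 |
| 11 | 0.848 | 0.918 |
| 12 | 0.880 | 0.938 |

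The stated 85% therefore needs 12 per group two-sided or 9 one-sided. At 10 per group, power is about 81% two-sided and 89% one-sided.

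**Step 4. What the same n would mean under the non-inferiority label.** The article gives no margin, so every margin M here is an assumption. With true difference 0, SD 18.55, one-sided 0.025 and 85% power, n per arm = 2 × 18.55² × (1.960 + 1.036)² / M²:

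| Assumed margin (points) | n per arm, one-sided 0.025 | n per arm, one-sided 0.05 |
|---|---|---|
| 5 | 248 | 198 |
| 10 | 62 | 50 |
| 15 | 28 | 22 |
| 20 | 16 | 13 |
| 24.7 | 11 | 9 |

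Turned round, 10 per arm gives 85% power only for a margin of about 22 to 25 points (normal approximation) or 23 to 26 (t), according to whether one-sided 0.05 or 0.025 is used. That is about as large as the whole benefit assumed in section 2.6.

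**Step 5. Precision, for illustration.** Assume an unadjusted two-sample comparison, 10 completers per arm and SD 18.5. The two-sided 95% half-width is 2.101 × 18.5 × √(2/10) = 17.4 points. A one-sided 95% limit on the same inputs lies 14.3 points from the estimate.

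**The case against.** The strongest reply is that this is one wrong word. The label appears once, in a descriptive sentence, and everything operative points to superiority. That is correct. A reader might infer from section 2.1 that the design cannot support the trial's conclusion, but the article does not bear that out, because the sizing and the test already serve the aim of benefit.

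A reader might also infer that the investigators plan to report a null result as non-inferior. No section says so. Section 2.9 reports interaction significance and Cohen d, so the risk lies in how the label could be used later.

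The article is condensed, and a missing margin or confidence-limit rule could be detail left to a fuller document. For that reason the absence is not charged separately. The contradiction stands without it, because section 2.6 gives the sample-size basis and that basis is a difference to detect. A margin stated elsewhere would not reconcile sections 2.1 and 2.6 without a new rationale for n.

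Finally, the 17-point figure is easily over-read as saying that any null result is compatible with 17 points of worsening. It applies only when the observed difference is exactly zero. With an observed 10-point benefit, the limit would be about 17.4 − 10 = 7.4 points of worsening. The planned ANCOVA uses covariates, and more than 10 per arm might complete, so the real interval may differ. These limits are accepted, and the figure is kept as an illustration only.

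**Conclusion.** The point holds as an internal contradiction in the stated hypothesis. Section 2.1 declares non-inferiority, while the aim, the sample size and the test are superiority, and nothing in the article reconciles them. Because the declared hypothesis decides how a null result may be read, this is more than a clerical matter, even though the correction is small.

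Relabelling leaves the 10 and 13 per group as they stand. Keeping the label would require a margin and a new justification of n. Under the assumptions of the illustration, an observed difference of zero could not support a non-inferiority claim with a margin below about 17 points (about 14 if judged by a one-sided 95% limit).

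Naming the hypothesis also brings out the unstated sidedness in section 2.6. Under a two-sided t-test at 0.05 with d = 1.34, 10 completers per group give about 81% power rather than 85%.

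**What to change.** 1. In section 2.1, replace non-inferiority with superiority.
2. Add one sentence saying that a non-significant result will not be interpreted as non-inferiority or equivalence.
3. State in sections 2.6 and 2.9 whether the test is one- or two-sided. If it is two-sided at 0.05, restate the power for 10 completers per group as about 81% (t-test, d = 1.34). Keeping 85% would need 12 completers per group.

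Items 1 and 2 cost one word and one sentence and change no procedure. Item 3 is also only text if the lower power is accepted. It affects recruitment only if the team chooses to hold 85% with a two-sided test.

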### 2.2. Eligibility Criteria

The inclusion criteria for participants allocated to both control and intervention groups are as follows: To become a participant in this study, women need to declare a premenopausal status, hold a clinical diagnosis of endometriosis (by laparoscopy or magnetic resonance imaging), have a clinical history of endometriosis-related symptoms, be able to walk without assistance and to read and write enough, be capable and willing to provide consent and to be interested in improving their lifestyle.

However, we will exclude those women with acute or terminal illness, a recent fracture in any upper or lower extremity (<3 months), disc herniation and any chronic disease or orthopaedic issues that would interfere with her ability to participate in a physical activity program, as well as those that express unwillingness to complete the study requirements and those involved in other exercise program.

### 2.3. Intervention

#### 2.3.1. Exercise Intervention Group

‘Physio-EndEA’ is a 9 (1 + 8)-week supervised tailored program of therapeutic exercise that incorporates global and lumbopelvic exercises that was designed by a multidisciplinary team. It combines aerobic, resistance and stretching exercises with a core stabilization perspective. The intervention will be performed in small groups of 4–6 participants, training 90 min/session twice a week. Sessions are designed, carefully supervised, guided and instructed by a qualified group of physiotherapists and physical exercise specialists with more than 5 years of experience in therapeutic exercise in oncology and related diseases.

The intervention planning is shown in Table 1. The first part of the program, with a single week duration, consists of individual sessions for initial training of motor control by using both rehabilitative ultrasound imaging (RUSI) [53] and a Stabilizer^®^ Pressure Biofeedback (Chattanooga, Hannover, Germany). For that, patients will be initially RUSI-guided to selective pre- or co-activate both TrA and pelvic floor muscles through the abdominal drawing-in manoeuvre (ADIM), as previously suggested [54,55]. This method facilitates both patient learning and clinician verification of TrA muscle recruitment pattern. After that, a trained physiotherapist teaches a sort of stabilization exercises with and without Stabilizer^®^. Patients are invited to repeat this list of exercises twice daily (>5 min each) during that week. Patient will not progress to the second part of the program until the physiotherapist verifies motor control with RUSI through the ability to pre-/co-activate and maintain contraction of TrA and pelvic floor muscles during basic lower-limb exercises. Moreover, during the following 2 weeks, patients are encouraged to continue with home-based biofeedback exercises.

The second part of the intervention will lasts 8 weeks with group sessions twice per week focused on health-related fitness and motor control improvement. Each session will be divided into three sections: (1) an initial period with warm-up exercises (10 min); (2) a main period with aerobic (20–40 min) (continuous brisk walks), stretching (10–15 min) and lumbopelvic stabilization exercises (30–35 min) (taking into consideration the instructions previously learnt about motor control); and a final cool-down period of breathing and relaxation exercises. Details of the specific lumbopelvic stabilization exercises that these participants will perform are summarized in Table 1’s footnotes. Increases in both duration and intensity for aerobic exercises will be carried out based on fatigue perception. Alternatively, duration, intensity and number of repetitions for resistance exercises will be sequentially increased over time based on the adequate motor control of the lumbopelvic area, as well as fatigue perception. For that, by using the Borg Fatigue Scale [56], the physiotherapist (aided by two technicians) will daily inform about the maximum level of perceived fatigue that each patient must assume (from <11 at initial week to 13–14 at the end of the program), and thus, the women will increase or decrease the exercise intensity accordingly. For that purpose, women will be previously instructed with this scale to appropriately report their current perceived fatigue.

Adherence is defined based on the patient’s attendance to the sessions, considering as dropouts when they do not participate in at least 12 (75%) of 16 scheduled sessions. To maximize adherence, some strategies will be implemented, including adapted timetables to patient needs, music in all sessions and telephone calls following missed sessions.

